# Effectiveness of the Epley’s maneuver performed in primary care to treat posterior canal benign paroxysmal positional vertigo: study protocol for a randomized controlled trial

**DOI:** 10.1186/1745-6215-15-179

**Published:** 2014-05-21

**Keywords:** Primary care, Canalith repositioning procedure, Benign paroxysmal positional vertigo, Randomized clinical trial, Betahistine

## Abstract

**Background:**

Vertigo is a common medical condition with a broad spectrum of diagnoses which requires an integrated approach to patients through a structured clinical interview and physical examination. The main cause of vertigo in primary care is benign paroxysmal positional vertigo (BPPV), which should be confirmed by a positive D-H positional test and treated with repositioning maneuvers. The objective of this study is to evaluate the effectiveness of Epley’s maneuver performed by general practitioners (GPs) in the treatment of BPPV.

**Methods/Design:**

This study is a randomized clinical trial conducted in the primary care setting. The study’s scope will include two urban primary care centers which provide care for approximately 49,400 patients. All patients attending these two primary care centers, who are newly diagnosed with benign paroxysmal positional vertigo, will be invited to participate in the study and will be randomly assigned either to the treatment group (Epley’s maneuver) or to the control group (a sham maneuver). Both groups will receive betahistine. Outcome variables will be: response to the D-H test, patients’ report on presence or absence of vertigo during the previous week (dichotomous variable: yes/no), intensity of vertigo symptoms on a Likert-type scale in the previous week, total score on the Dizziness Handicap Inventory (DHI) and quantity of betahistine taken.

We will use descriptive statistics of all variables collected. Groups will be compared using the intent-to-treat approach and either parametric or nonparametric tests, depending on the nature and distribution of the variables. Chi-square test or Fisher’s exact test will be conducted to compare categorical measures and Student’s *t*-test or Mann–Whitney *U*-test will be used for intergroup comparison variables.

**Discussion:**

Positive results from our study will highlight that treatment of benign paroxysmal positional vertigo can be performed by trained general practitioners (GPs) and, therefore, its widespread practice may contribute to improve the quality of life of BPPV patients.

**Trial registration:**

ClinicalTrials.gov Identifier: NCT01969513.

## Background

Dizziness, a common complaint in patients presenting to the primary care office and the emergency department, is a disorder of spatial orientation. Approximately 3% of the visits to US emergency departments were accounted for by dizziness presentations according to data from a nationally representative study [1].

Vertigo is a subtype of dizziness, defined as an illusion of motion caused by a mismatch of information from the visual, vestibular and proprioceptive systems. Vertigo is divided into central and peripheral causes. Central vertigo is generally more serious, whereas peripheral vertigo is usually benign. It has been estimated that 45 to 54% of the patients who attend the primary care physician with dizziness are suffering from vertigo [2]. The three most common causes of vertigo (accounting for 93% of all patient presentations) are: acute peripheral vestibulopathy (vestibular neuritis and labyrinthitis), Ménière’s disease and benign paroxysmal positional vertigo (BPPV), the latter being the most frequent [3].

The mean age of onset of BPPV is 49 years, its lifetime prevalence is approximately 2.4%, and its cumulative incidence reaches almost 10% at the age of 80 years [4]. The theories that try to explain the pathophysiology of BPPV are based on clinical and histopathologic findings. BPPV occurs as a result of displaced otoconia, which are small calcium particles (otoliths), normally attached to the otolithic membrane in the utricle. Because of trauma, infection, aging, and even without any known cause, otoliths can detach from the utricle and collect within the semicircular canals [5]. The posterior canal is the most frequently affected of the three semicircular canals. Movement of the head causes these otoliths to inappropriately trigger the receptors in the semicircular canals and send false signals to the brain, causing vertigo and nystagmus, as occurs during the Dix-Hallpike (D-H) maneuver.

The diagnostic approach to vertigo relies on the quality of symptoms reported. Patients suffering from vertigo may be diagnosed by asking the following question: ‘When you are dizzy, do you have a sense that you or your surroundings are spinning or moving?’ An affirmative response makes the diagnosis of vertigo most likely and directs the physician towards a subsequent search for vestibular causes. In the case of BPPV, patients may also present with lightheadedness, unsteadiness, loss of balance, blurred vision, nausea and vomiting, without hearing loss or tinnitus. Abnormal rhythmic eye movements (nystagmus) usually accompany the symptoms of BPPV. Signs and symptoms may come and go, with symptoms frequently lasting from 10 to 30 seconds. Some patients, however, may feel vertiginous for several minutes and the imbalance and nausea may last several hours. The average duration of each episode is two weeks but a third of patients refer episodes longer than a month. Forty-four percent of BPPV cases experience a single episode of dizziness while 56% are recurrent [4]. Activities that bring about the signs and symptoms of BPPV can vary from person to person, but are almost always brought on by a change in the position of the head: turning in bed, neck extension and tilting the head forward. Although rare, it is possible to have BPPV in both ears (bilateral BPPV).

Physical examination is the next and the last step to make an accurate diagnosis. The equipment needed for the physical examination is simple and available in every primary care examination room: stethoscope, otoscope, sphygmomanometer, reflex hammer, tuning fork and a flat examining bed. Coupled with the medical history and physical examination, the Hallpike maneuver (also known as Dix-Hallpike test or) is extensively used in both the diagnosis and short- and long-term control of BPPV. The maneuver is performed on a flat examination table. While the patient is in a seated position, the physician turns the patient’s head 45° to one side, then rapidly, but smoothly lays the patient into a supine position with the head hanging about 20° over the end of the table and observes the patient’s eyes for approximately 30 seconds. The maneuver is repeated with the head turned to the opposite side. The result is positive if the patient develops symptoms (vertigo) and nystagmus. It has a positive predictive value of 83% and a negative predictive value of 52% [3] (Additional file 1: Video 1 Dix-Hallpike maneuver).

Most patients with vertigo have benign disorders and can be successfully managed by the primary care physician. A low percentage of the disorders require laboratory testing, advanced testing or referral to a specialist [6].

Treatment options include watchful waiting, vestibulosuppressant medication, vestibular rehabilitation, canalith repositioning and surgery. Among these treatment modalities, canalith repositioning procedures (CRPs) are the first choice treatment for BPPV. The aim of CRPs is to move the displaced otoliths from the semicircular canal back to the utricle where they belong. Another less effective treatment and more time consuming technique, the Brandt-Daroff exercise, consists of lying down on your side and then getting up quickly. The presumed mechanism for this therapy is to loose and disperse particles from the cupula of the posterior semicircular canal. The aim of this exercise is habituation and compensation of the vestibular system; it does not prevent recurrence and is not always well tolerated.

Out of all the CRPs, the Epley’s maneuver has been the most successfully used, and is particularly indicated in the treatment of posterior canal BPPV. It consists of a series of four quick movements of the head and body from sitting to lying, rolling over, and back to sitting. Each position is maintained for at least 30 seconds or until positional nystagmus ceases [7] (Additional file 2: Video 2 Epley’s maneuver). A meta-analysis of three high-quality clinical trials demonstrated the effectiveness of the Epley’s maneuver in short-term follow-up, measured in terms of the Hallpike test (D-H test) turning negative (odds ratio (OR) = 5.67; 95% confidence interval (CI) 2.21 to 14.56). This meta-analysis concludes that further research in this field should consider the following criteria: 1. The use of a rigorous randomization technique with respect to adequate pre-allocation concealment; 2. The blinding of outcome assessors; 3. The inclusion of a post treatment Hallpike maneuver as a part of the reported results; and 4. Long-term follow-up of patients [8]. Another meta-analysis came to the same conclusions [9]. Little evidence exists to demonstrate any benefit of the Epley’s maneuver in long-term follow-up [10].

This maneuver has proved to be useful in both pediatric [11] and older-aged patients [12] and appears to be safe and effective if the following few contraindications are considered: cervical spinal stenosis, severe kyphoscoliosis, limited cervical mobility, Down syndrome, advanced rheumatoid arthritis, cervical radiculopathies, Paget’s disease, morbid obesity, ankylosing spondylitis, severe lumbar dysfunction and spinal cord injuries. No serious adverse effects have been reported.

The Epley’s maneuver can be performed by general practitioners (GPs). Although most clinical trials on the effectiveness of this maneuver have taken place in specialized clinics, one study conducted in a primary care center demonstrated that trained GPs achieved the same results as the specialists in terms of D-H test turning negative. However, this study could not prove the subjective improvement of the patients compared to the control group [13].

Several authors emphasize the need for more research to be performed in the primary care setting. One article regrets the slow implementation of the results of scientific evidence, highlighting that in Germany only 8% of patients are treated with repositioning maneuvers, and recommending the practice of the D-H and Epley’s maneuvers to these physicians [14]. A study in Israel demonstrated that only 25% of patients with BPPV referred to a specialist had been correctly diagnosed by their doctors and that in most cases, the correct diagnosis had been made by otolaryngologists (ENT specialists). Out of the 120 patients studied, only 2 cases (the 2 submitted by ENT specialists) had undergone the D-H maneuver to reach the diagnosis [15]. A study conducted in Spain found that the average duration between the onset of symptoms and initiation of treatment with canalith repositioning maneuvers in a specialized ENT center was 20 weeks and that only 1 patient out of 60 was correctly diagnosed as BPPV [16]. Moreover, the duration of the illness before receiving Epley’s maneuver was considered the only independent predictor of recurrence according to a long-term follow-up study. A systematic review also recommends that more research be performed and emphasizes that such investigation should include different specialists, other than otolaryngologists or neurologists, such as GPs [17].

Therapy with betahistine dihydrochloride has been widely prescribed in patients with vestibular disorders for symptomatic treatment of vertigo, and especially in Ménière’s disease patients. A meta-analysis undertaken to evaluate the efficacy of betahistine in the treatment of other vertiginous syndromes, such as BPPV (cupulo-canalilithiasis), analyzed seven double-blind, placebo-controlled, randomized studies, and confirmed betahistine’s therapeutic benefit and effectiveness [18]. Several other studies have proved that the combination of betahistine and repositioning maneuvers improve outcomes, in comparison to maneuvers alone [19,20] but its use for BPPV remains controversial [21].

To date, no relevant studies have been performed on the impact of the use of the Epley’s maneuver in primary care settings, in terms of temporary disability (number of episodes and duration), duration of the drug treatment with its subsequent side effects, referral to specialists, number of recurrences and quality of life.

Our clinical trial will be conducted in a primary care setting, and will study the condition at its earliest stages, when patients are more likely to attend our practices, and where the literature is less conclusive. In addition, response to treatment will be evaluated at one month and at one year after inclusion in the study. The effectiveness of the Epley’s maneuver in the remission of symptoms during the first week may reduce the course of vertigo, and may result in improvement of quality of life, temporary disability and decrease in the amount of medication taken.

## Methods/design

### Hypothesis

The Epley’s repositioning maneuver, performed by GPs, is effective in the short, mid and long term for the treatment of BPPV. We expect to find a significant difference of 30% or over in the negativization of the D-H test in the intervention group (Epley’s maneuver) compared to the control group (a sham maneuver), as well as in the clinical improvement of the patients.

### Aim

#### Primary objective

The study’s primary objective is to determine whether the intervention group (Epley’s repositioning maneuver) improves clinically as compared to the control group (a sham maneuver), after a week, a month and a year of follow-up (second, third and fourth visit respectively). Definition of clinical improvement will include negativization of the D-H maneuver, improvement in the subjective perception of vertigo, quality of life and amount of betahistine tablets that the patients report to have taken.

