#### Secondary objectives

We will analyze whether there is a statistically significant clinical improvement in the intervention group in comparison to the control group in terms of:

1. Negativization of the D-H test at a week, a month and a year follow-up.

2. Answer to the dichotomous (yes/no) question regarding presence of vertigo in the previous week.

3. Number of new episodes of vertigo between medical visits.

4. Time from the baseline visit to the first new episode.

5. Rate of vertigo severity on a 10 point-Likert scale: 0 = no symptoms of vertigo; 10 = most severe and unbearable.

6. Quality of life measured with the specific questionnaire Dizziness Handicap Inventory- Short form (DHI-S).

7. Amount of betahistine tablets taken, according to the patients’ self-registers.

8. Days of temporary disability due to vertigo or other causes, recorded on the electronic medical record.

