### Visit 1 for patients in the intervention group arm

The Epley’s maneuver will be performed only in the first visit since a single procedure has been shown to improve the condition in 76% of patients [25]. Moreover, most patients may improve spontaneously after a month, regardless of which group they were assigned. The maneuver consists of five sequential positions of the head and body, performed with the aim to move the displaced canaliths from the semicircular canal back to the utricle where they no longer cause symptoms. There is some controversy over whether postural restrictions for a few days after this procedure are beneficial for the patient and can improve outcomes [26]. However, we have decided not to include these restrictions in our study as they are poorly tolerated and can hamper the comparability between groups [27].

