Statistical analysis will be carried out by statisticians from the Institut Universitari d’Investigació en Atenció Primària Jordi Gol (IDIAP Jordi Gol), who will have an advisory role. Data will be introduced into a SPSS version 18.0 system database (SPSS Inc, Chicago, IL, USA). Descriptive analysis, and statistical hypothesis testing, will also be conducted with the SPSS version 18.0 system, with blinding. The level of statistical significance will be set at 0.05 and all tests will be two-tailed. All known potential confounding factors will be measured at the beginning of the study and comparison between the control and the intervention groups will be carried out adjusted for these known confounders.

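### The primary objective is four components at three visits with no rule for what counts as success, and the same components are listed again as secondary objectives.

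*Protocol article*

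**What the plan says.** Under Primary objective, the intervention group is to be shown to improve clinically "after a week, a month and a year of follow-up (second, third and fourth visit respectively"). The content of that improvement is given as: "Definition of clinical improvement will include negativization of the D-H maneuver, improvement in the subjective perception of vertigo, quality of life and amount"; the amount meant is the number of betahistine tablets taken. That makes four components at three visits. None is placed first and no combining rule follows.

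Under Secondary objectives, the lead-in is "We will analyze whether there is a statistically significant clinical improvement in the intervention group in comparison to the control group in terms of" eight items. Four of the eight topics are the primary components again:

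- Objective 1: "Negativization of the D-H test at a week, a month and a year follow-up".
- Objectives 2 and 5, two versions of perceived vertigo: "Answer to the dichotomous (yes/no) question regarding presence of vertigo in the previous week" and "Rate of vertigo severity on a 10 point-Likert scale".
- Objective 6: the short-form Dizziness Handicap Inventory (DHI-S).
- Objective 7: betahistine tablets.

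Statistical analysis assigns methods by objective number, and adds a logistic model for a cured/not cured variable that is not linked to any component or visit. It closes with "The level of statistical significance will be set at 0.05 and all tests will be two-tailed".

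Sample size sets improvement rates of 30% (control) and 55% (intervention), two-sided alpha 0.05, beta 0.2, 20% loss and about 75 per group. It attaches this to objectives 1 and 2 and does not name the visit.

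**The concern.** A reader of the results must be able to tell from the protocol which single result, or which stated combination, decides the trial. Here that cannot be done. The same outcome also cannot both decide the trial and be secondary. A multiplicity method may be left to an analysis plan; the choice of primary outcome and visit belongs in the protocol, and this article does state one, in a form that leaves it open.

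The stake is that the decisive comparison could be chosen after the data are seen. The stated 80% power also belongs to no identified visit. That matters because the expected control rate changes with time: the Background reports that a third of patients have episodes longer than a month, and the section on visit 1 for the intervention arm says that "most patients may improve spontaneously after a month, regardless of which group they were assigned".

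**Working it through.** **1. Reproduce the stated sample size.** Inputs (Sample size section): p1 = 0.30, p2 = 0.55, two-sided alpha 0.05, power 0.80, loss 20%.

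- Arcsine formula: h = 2·asin(√0.55) − 2·asin(√0.30) = 0.5117. n = 2·[(1.960 + 0.842)/h]² = 59.96 per group, and 59.96/0.8 = 74.9. This matches the stated 75.
- Pooled-variance formula: 61 evaluable per group, and 61/0.8 = 77, close to 75.
- Power with 75 × 0.8 = 60 evaluable per group: Φ{[0.25·√60 − 1.960·√(2·0.425·0.575)] / √(0.30·0.70 + 0.55·0.45)} = Φ(0.837) = 79.9%.

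The size is therefore right for one binary comparison, at one visit, at 0.05.

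**2. Count the comparisons.** Four components × three visits = 12. If both versions of perceived vertigo are used, 5 × 3 = 15.

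**3. Chance of at least one false positive, if any one significant result counts as success.** Under independence it is 1 − 0.95^k:

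| Reading | k | Chance |
|---|---|---|
| One outcome (or one composite) at three visits | 3 | 14.3% |
| Four components at one visit | 4 | 18.5% |
| Four components at three visits | 12 | 46.0% |
| Both vertigo versions, three visits | 15 | 53.7% |

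The tests are made on the same patients, so they are correlated. The article gives no correlations, so these are assumptions. Simulated, for the 12 tests:

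| Assumed correlation | Equal for all pairs | Same value between outcomes and between visits, multiplied when both differ |
|---|---|---|
| 0.3 | 40% | 42% |
| 0.5 | 32% | 36% |
| 0.7 | 23% | 27% |
| 0.9 | 13% | 15% |

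Counting only false positives in favour of Epley's maneuver, the independent figure is 1 − 0.975^12 = 26%, against 2.5% for a single test. Under the second structure it runs from 22% (correlation 0.3) to 7.5% (0.9).

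If every component had to be significant at a fixed visit, the chance would not exceed 5%.

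**4. Power if all 12 stayed as alternative routes to success.** Bonferroni alpha = 0.05/12 = 0.00417. Power at 60 evaluable per group for 30% v 55% falls to 46%. Restoring 80% needs 106 evaluable, or 106/0.8 = 133 per group.

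**5. What can be said about power at one month.** Assume, for illustration only, a control rate of 67% (one minus the third whose episodes outlast a month). The formula of step 1 with 60 per group gives:

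- Planned odds ratio kept: (0.55/0.45)/(0.30/0.70) = 2.85, so 67% v 85%; power about 66%.
- Planned 25-point difference kept: 67% v 92%; power about 93%.

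The two readings fall on either side of 80%.

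**The case against.** The text does hint at an intended primary. The Hypothesis leads with the D-H test turning negative, the sample size is attached to objectives 1 and 2, and the Background singles out remission in the first week. On this view the fault is only a missing label. That stands as a reason why the repair is easy, but no section designates the D-H test as primary, and the visit stays open in all of them.

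The any-one-of-12 rule is also not in the article. The Hypothesis claims effect in the short, mid and long term, and for the D-H test together with clinical improvement, which can be read as requiring everything. That objection stands. A reader might infer that the trial's false-positive rate is 46%. The documents do not support that as a fact: it is the independent case under one possible success rule, and strong correlation brings it down to about 13%.

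A reader might also infer that 80% power cannot hold at one month or one year. This is not supported either. The third quoted in the Background is patient-reported episode duration, not D-H negativity after a baseline visit in patients selected for a positive test, and the article says only that most patients may improve. No one-year rate for this endpoint is given. Whether power rises or falls depends on which effect measure is held constant.

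**Conclusion.** The point holds. The primary objective is stated, but as an unranked set of components and visits that reappears under the secondary objectives, with 0.05 for every test and a sample size attached to objectives labelled secondary at an unnamed visit. As written, nothing defines whether the trial succeeded.

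The error inflation is conditional. If any significant comparison may be claimed, it is 46% for 12 independent tests and about 13% to 42% for assumed correlations of 0.9 to 0.3. Even one outcome at three visits gives up to 14%. Under a rule requiring all components there is no inflation. Since no rule is stated, the actual rate is undetermined.

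The 30% control rate is tied to no visit and is doubtful at one month on the article's own remarks. Power there is undetermined: about 66% to 93% at 60 per group for an assumed 67% control rate. The sample size itself is not wrong for a single comparison. The main finding does not depend on the power at later visits.

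**What to change.** Before unblinded data are seen:

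1. Name one primary outcome at one visit, tested by intention to treat at two-sided 0.05. A negative D-H test at one week (visit 2) is the option best supported by the Background, the Hypothesis and the Sample size section; the choice is the investigators'.
2. Tie the 30% v 55% calculation to that outcome and visit. With 75 per group and 20% loss, power is about 80% for those rates, so no extra patients are needed.
3. Remove that comparison from the secondary list.
4. Make all remaining outcome-by-visit comparisons of these components secondary: 15 − 1 = 14 if both the yes/no vertigo question and the severity scale are kept. Either test them in a fixed sequence that names the visit for each step, or report them with confidence intervals and no confirmatory claim.

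The cost is protocol and analysis plan wording only. The downside is that the later visits and the patient-reported outcomes lose primary status.
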